**Figure 2 F2:**
[figure not shown]
**Screenshot of the MBC task worksheets. ***Note.* Each practice change will have an Excel workbook that has a separate worksheet for each of three scenarios (*i.e.,* Scenario A, Scenario B, Scenario C), with each practice context having different barriers and facilitators. Several features support multifaceted decision-making while completing the task. First, all of the discrete implementation strategies developed in ERIC Stage 1 will be listed in the first column, and sorted into categories based on ERIC Stage 2 Concept Mapping data. Further, for each strategy, a comment box containing the definition for the term appears when the participant moves their cursor over the strategy’s cell. In Figure 2, the ‘Conduct local consensus discussions’ (cell A15) definition box has been made visible. Second, the participant response options are provided in a drop-down menu format to prevent data entry errors. In Figure 2, cell H6 has been selected so the drop-down menu is visible. Third, participants will be encouraged to complete their recommendations for Scenarios A through C sequentially. After the recommendations have been made for Scenario A, these will remain viewable on the worksheet for Scenario B, and the recommendations for Scenarios A and B remain viewable on the Scenario C worksheet, as seen in Figure 2. This supports the participants in efficiently making recommendations considering the current context (Scenario C) while comparing and contrasting these recommendations with those provided for Scenarios A and B, where different combinations of barriers and facilitators are present. Finally, different hues of the response columns are used to visually separate the recommendations for the three contexts with ‘Pre-implementation’ having the lightest shade and ‘Sustainment’ having the darkest.

Within each scenario of each practice change, a Relative Essentialness Estimate (REE) will be calculated for each discrete implementation strategy to characterize participant recommendations. REEs are based on aggregate zero-centered log-count analyses of the recommendation frequency data. This type of analysis provides a nonparametric characterization of the observed frequency of recommendations where a value of 1 represents the highest recommendation rate and 0 represents the lowest recommendation rate for the sample. This type of analysis will be used because it is appropriate for studies with 20 or more participants [73,74]. In Stage 4, REEs for each strategy will be presented to participants accompanied by the corresponding importance and feasibility ratings obtained in Stage 2 (context independent ratings). Count-based analyses will be used to characterize the most commonly selected combinations of essential strategies for each scenario, and graphical and descriptive analyses of these counts will also be presented in Stage 4. The relationship between discrete strategies as compliments or substitutes will be analyzed through dividing the actual joint probabilities of strategies by expected joint probabilities (assuming independence) [73]. Complementarity and substitutability numbers will be used as discussion points in Stage 4.

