The empirical evidence for specific implementation strategies is difficult to summarize because of the large number of strategies listed in the literature and the lack of consistency of their defined features [5]. A recent paper identified 68 discrete implementation strategies [9]. This high number of strategies presents implementation researchers and clinical managers with the challenge of deciding which ones are relevant strategies to meet their particular implementation goals. Market researchers have developed an approach to address these complex types of decisions that involve a wide array of choices using ‘choice menus.’ Choice menus structure options in a way that allow decision-makers to consider a large range of choices in building their own products or solutions. As a result, mass customization of consumer products has expanded greatly over the last decade [29]. Choice menus highlight a trade-off: more choices give decision-makers greater flexibility but simultaneously increase the complexity (*i.e.*, cognitive burden) of making decisions [30]. However, decision-makers with high levels of product expertise consider large choice menus less complex than do consumers with low levels of product expertise [31]. Likewise, choice menus can be used to structure large numbers of implementation strategies, particularly when used by decision-makers with expertise in implementation. Given the level of content expertise implementation scientists and clinical managers bring to quality improvement initiatives, choice menus can be an effective tool for selecting among the dozens of potentially relevant implementation strategies for a particular change initiative.

In the absence of empirical evidence to guide the selection of strategies, one might turn to the considerable number of theories and conceptual models pertaining to implementation in order to guide the selection of strategies [32,33]. However, reviews of the published literature have found that theories and models have been drastically underutilized [23,34,35]. This limits our ability to understand the mechanisms by which implementation strategies exert their effects, and ultimately, how, why, where, when and for whom implementation strategies are effective. The underutilization of theory may also be indicative of limitations of the theories and models themselves [36,37], and signal the need to develop more pragmatic tools that can guide the selection of implementation strategies in practice settings.

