## Methods/Design

### Overview

The ERIC process involves a four-stage sequential mixed methods design (qualitative → QUANTITATIVE) [57]. Stages 1 and 2 are used to establish expert consensus on a common nomenclature for implementation science (Aim 1). Stages 3 and 4 build upon the earlier stages and are used to develop expert recommendations regarding how to best match discrete implementation strategies to high priority implementation scenarios in mental health (Aim 2). Table 1 provides an overview of the study’s aims and stages. Qualitative methods are used to develop expert recommendations, and quantitative methods are used to guide the recommendations by obtaining ratings of implementation strategies (alone and as applied to example implementation scenarios), providing structured feedback to the expert panel, and characterizing the consensus process.

**Table 1 T1:** Overview of the four stages of the ERIC process

	**Stage**	**Input**	**Task**	**Output**
**Aim 1**	Stage 1	Refined compilation of discrete implementation strategies	Modified Delphi, 2 feedback rounds and consensus meeting	•Expert consensus on key concepts (definitions & ratings)
	Modified Delphi			
	Stage 2	Post-consensus compilation of discrete implementation strategies	Sort the strategies in to subcategories; rate each strategy in terms of importance and feasibility	•Weighted and unweighted cluster maps
	Concept Mapping			•Ladder maps
				•Go-zone graphs
				•Importance and feasibility ratings for each strategy
**Aim 2**	Stage 3	•Discrete implementation strategies	Essential ratings are obtained for each strategy for three temporal frames given each scenario	For each practice change:
	Menu-Based Choice	•Practice change narrative		•Relative Essentialness Estimates for each strategy given each scenario
		•Narratives of contextual variations of practice change scenarios		•A rank list of the most common strategy recommendation combinations
				•A summary of strategies that may serve as compliments and substitutes for each other
	Stage 4	•Menu-Based Choice data summaries for each scenario	Facilitated discussion; live polling of consensus reached during discussion	For each practice change:
	Facilitated Consensus Meeting	•Importance and feasibility ratings from the concept mapping task		•Expert consensus regarding which discrete implementation strategies are of high importance
				•Context specific recommendations

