### Study participants

Purposive sampling will be used to recruit an Expert Panel composed of implementation science experts and VA mental health clinical managers to participate in each of the four stages. The Expert Panel will be recruited using a snowball reputation-based sampling procedure in which an initial list of implementation science experts will be generated by members of the study team. The study team will target members of several different groups based on their substantial expertise in implementation research. These groups include: the editorial board for the journal ‘Implementation Science,’ implementation research coordinators (IRCs) for VA QUERIs [4], and faculty and fellows from the Implementation Research Institute [58]. Nominees will be encouraged to identify peers with implementation science expertise as well as clinical management expertise related to implementing EBBPs [59]. The groups identified to seed the snowball sampling method will be intentionally diverse to ensure adequate recruitment of VA and non-VA implementation experts. This approach to recruit a purposive sample is consistent with the qualitative methods employed in the study design [60].

Recruitment will target 25% to 50% clinical manager representation to ensure that recommendations in Aim 2 reflect the expertise of both scientists and clinical managers. The minimum total enrollment target for the Expert Panel is 20. There are only marginal increases in the reliability of expert consensus methods after sampling crosses the threshold of 12 participants [61], and a minimum enrollment of 20 should ensure adequate saturation in qualitative analyses for the expert consensus and recommendation meetings in Stages 1 and 4 [62]. Implications of this sample size target for Stages 2 and 3 will be discussed as their respective methods are presented. Only individuals residing in the four primary time zones of North America (*i.e.*, Eastern through Pacific) will be recruited to minimize scheduling conflicts for the live webinar portions of the study.

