In the MBC tasks, panelists will indicate how essential each discrete implementation strategy is to successfully implement the practice changes described in each narrative, taking care not to burden the care system with unnecessary implementation tasks. Essential ratings (*i.e.*, absolutely essential, most likely essential, most likely inessential, absolutely inessential) will be dichotomized as essential and inessential for primary analyses used for panelist feedback. Panelists will provide essential ratings separately for three temporal frames (*i.e.*, pre-implementation, implementation, and sustainment) for each scenario. Strategies will be organized into clusters consistent with the categories identified in Stage 2 to help decrease the cognitive burden of this task [72]. This information will be placed in structured spreadsheets that support participants in considering multiple implementation strategies simultaneously. This structure is designed to improve participants’ ability to consider each strategy recommendation in relation to similar strategies while being able to view whether their recommendations are consistent or change based on timing and contextual features of each scenario (see Figure 2).

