### Stage 4: Web-based facilitated expert recommendation process

A live web-based facilitated expert recommendation process will be employed in Stage 4. Separate webinars will be hosted for each of the three practice changes. Prior to the webinar, respondents will be provided with the following materials for each scenario: a description of the scenario for continued reference; a personal summary of the essential ratings he or she provided for each implementation strategy at each temporal phase of implementation; and group data describing numerical and graphical descriptive analyses of the most commonly selected combinations of essential strategies, itemization of strategies qualifying as substitutes or compliments, the REE of each strategy, and Stage 2 importance and feasibility ratings of each strategy. During the interactive webinar, study investigators will facilitate a general discussion of the summary material provided to panelists in preparation for developing recommendations for which implementation strategies are essential at each of the three temporal phases in the particular scenarios. This will be followed by scenario-specific facilitated discussions of the top five essential strategy combinations obtained in Stage 3. Live polling will be used to document the degree of consensus for the final recommendations for each scenario. Polling will commence one scenario at a time, addressing each temporal phase of implementation separately, one conceptual cluster of strategies at a time, presenting the top five essential strategy combinations plus any additional combinations identified as highly preferable during the facilitated discussion. Poll results will be used to characterize the expert panel’s rate of consensus for the final set of recommendations regarding which discrete strategies are essential for each phase of implementation for a particular implementation scenario.

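### The raw observed/expected ratio used to list complements and substitutes is imprecise at the minimum panel of 20 and is biased towards complements when panelists differ in how readily they say essential

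*Protocol article*

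**What the plan says.** The Stage 3 section (text after Figure 2) says the relation between two strategies will be analysed by "dividing the actual joint probabilities of strategies by expected joint probabilities (assuming independence". The ratings entering that calculation are binary: the four-level scale "will be dichotomized as essential and inessential for primary analyses used for panelist feedback". The same section says "Panelists will provide essential ratings separately for three temporal frames", within three scenarios per practice change; Stage 4 refers to three practice changes.

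The result is a named product. Table 1 lists among the Stage 3 outputs "A summary of strategies that may serve as compliments and substitutes for each other". The Stage 4 section includes in the pre-webinar material for each scenario an "itemization of strategies qualifying as substitutes or compliments". Stage 3 describes the numbers as points for discussion.

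On size, the Study participants section says "The minimum total enrollment target for the Expert Panel is 20". Stage 3 adds "This type of analysis will be used because it is appropriate for studies with 20 or more participants", but that sentence follows the description of the Relative Essentialness Estimate and supports that analysis. No similar support is given for the pairwise ratio. On the number of strategies, the Background says "A recent paper identified 68 discrete implementation strategies", and Stage 1 may change that list.

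**The concern.** There are two separate problems with the statistic.

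- **Precision.** With 20 panelists a joint count is a small integer, and one panelist more or less moves the ratio a long way. The same departure from 1 means very different things for rarely and widely endorsed strategies.
- **Bias.** Dividing by the product of the two marginal rates treats panelists as interchangeable. If some call many strategies essential and others few, any two strategies will tend to be chosen together by the generous raters. That is response style, not complementarity.

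At stake is the quality of one descriptive output. Panelists would receive a list, under the label of qualifying pairs, in which chance and response style cannot be told from real relations, just before they discuss which strategies belong together.

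**Working it through.** The article states no precision, cut-off or error rate for the ratio, so there is no figure to reproduce.

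**Inputs from the article:** n = 20 (minimum panel), 68 strategies (starting list), binary ratings. **Assumed, because the article does not give them:** endorsement rates, cut-offs, spread of leniency between panelists.

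**1. How coarse the ratio is.** If x and y panelists endorse the two strategies and k endorse both, R = (k/n) / [(x/n)(y/n)] = nk/(xy).

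- x = y = 10: R = 20k/100, so k = 4, 5, 6 gives 0.80, 1.00, 1.20.
- x = y = 6: R = 20k/36, so k = 1, 2, 3 gives 0.56, 1.11, 1.67.
- x = y = 14: R = 20k/196, so k = 9, 10, 11 gives 0.92, 1.02, 1.12.

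A single panelist shifts R by 0.20, 0.56 and 0.10 respectively.

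**2. Exact distribution for unrelated pairs.** Take x and y as binomial (at least 1) and k given x and y as hypergeometric. At n = 20 the central 95% range is about 0–2.5 at rates of 30%, 0.48–1.50 at 50% and 0.78–1.22 at 70%. With both strategies at the same rate:

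| Rate of both | SD of R, n = 20 | R ≤ 0.75 or ≥ 1.25, n = 20 | Same, n = 40 |
|---|---|---|---|
| 0.2 | 1.23 | 86% | 73% |
| 0.3 | 0.66 | 69% | 52% |
| 0.4 | 0.40 | 51% | 32% |
| 0.5 | 0.26 | 31% | 14% |
| 0.6 | 0.17 | 13% | 3% |
| 0.7 | 0.11 | 3% | <1% |
| 0.8 | 0.06 | <1% | <1% |

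Averaged over all pairs of rates from 0.2 to 0.8 at n = 20, the share flagged is 63% with cut-offs 0.9/1.1, 40% with 0.8/1.2, 34% with 0.75/1.25 and 19% with 0.67/1.5.

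**3. A panel with mixed rates.** Simulate 68 strategies whose log-odds of endorsement have SD 1 around a mean of −0.5, 0 or 0.5 (typical rates 38%, 50%, 62%), with panelists equally lenient. At 0.75/1.25 about 49%, 34% and 18% of unrelated pairs are flagged.

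**4. Leniency.** Let panelist i endorse with probability qᵢ, and let strategies be independent given the panelist. Then the expected joint rate is E(q²), the reference is E(q)², and

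R ≈ E(q²)/E(q)² = 1 + (SD/mean)².

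With an assumed SD of 0.20:

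- mean 0.3: 1 + 0.04/0.09 = 1.44
- mean 0.5: 1 + 0.04/0.25 = 1.16
- mean 0.7: 1 + 0.04/0.49 = 1.08

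In simulated panels of 20 at this spread, R ≥ 1.2 in 67%, 44% and 15% of unrelated pairs, and R ≤ 0.8 in 13%, 6% and 0.4%. Without leniency differences the two tails are nearly equal: 36%/36%, 20%/19% and 4%/3%.

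On the logit scale, with the mixed rates of step 3, about 54–55% of unrelated pairs exceed 1 when the between-panelist SD is 0.5, and 71–73% when it is 1. At n = 40 and SD 1 the share is 80–82%. The larger panel reduces noise around a centre that is still above 1.

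**5. Number of pairs.** 68 × 67 / 2 = 2,278 per analysis.

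**The case against.** The strongest reply is that this is a descriptive aid. The numbers only inform discussion, Table 1 hedges with *may*, and the final recommendations come from live polling on the five leading combinations. Those combinations are obtained from separate counts, not from this ratio. That is right, and it limits the consequence. It does not remove it: the Stage 4 discussion of this material is meant to prepare the recommendations, and combinations that find favour in discussion are added to the poll.

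A second reply is that the speaking of qualifying pairs implies a rule, which a fuller protocol or analysis plan may contain. That also stands, and the absence of a cut-off from the article is not treated as an error here. But the article does fix the statistic and its independence reference, and no cut-off on that ratio corrects the leniency bias.

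Third, 20 is a minimum. A larger panel does reduce the noise: at 50% endorsement the share outside 0.75/1.25 falls from 31% to 14% at n = 40. It does not reduce the bias.

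A reader might infer more than the article supports:

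- *About half of all unrelated pairs will be flagged.* This is not a property of the plan. It holds only for certain assumed rates and cut-offs; for pairs endorsed by 70% of the panel it is far too high.
- *Most listed pairs will be noise.* The calculations contain only unrelated pairs. The false share of the list also depends on how many real relations exist, which was not modelled.
- *Tens of thousands of comparisons.* 27 × 2,278 = 61,506 assumes a separate analysis for each phase. The outputs are described by scenario, so 9 × 2,278 = 20,502 fits the text equally well. Polling also runs cluster by cluster.

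**Conclusion.** The point holds for the statistic, with moderate consequence. At the minimum panel the unadjusted ratio cannot separate related from unrelated pairs when endorsement is low or middling, while for pairs endorsed by 70% or more chance alone rarely produces a large departure from 1. Under cut-offs of 0.75/1.25 and no leniency differences, the flagged share of unrelated pairs is about 18–49% across the three assumed settings of endorsement rates.

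The direction of the leniency bias is certain whenever panelists differ: towards false complements and hidden substitutes. Its size is not known from the article. It is small at a between-panelist SD of 0.5 logit and substantial at 1. The article gives no ground for saying that the final recommendations would be wrong.

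**What to change.** In the Stage 3 paragraph that defines the ratio, replace the independence expectation with a permutation reference. Repeatedly reshuffle the panelist-by-strategy table of essential ratings while keeping every panelist's number of essential ratings and every strategy's total fixed, and use the mean joint count over the reshuffled tables as the expected value. Report each ratio with its permutation interval. In Stage 4, itemize only pairs outside their interval, and label the list exploratory.

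A 95% interval would still pass up to about 0.05 × 2,278 ≈ 114 unrelated pairs per analysis, so the label matters. False-discovery-rate control or a minimum expected joint count would shorten the list further. Both are optional for a discussion aid: an expected count of 5 at n = 20 already needs about 50% endorsement of each strategy (20 × 0.5 × 0.5), and either rule could empty the list.

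The cost is a short script on data already being collected, with no extra work for panelists, and a shorter list.

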### Stage 4: Web-based facilitated expert recommendation process

A live web-based facilitated expert recommendation process will be employed in Stage 4. Separate webinars will be hosted for each of the three practice changes. Prior to the webinar, respondents will be provided with the following materials for each scenario: a description of the scenario for continued reference; a personal summary of the essential ratings he or she provided for each implementation strategy at each temporal phase of implementation; and group data describing numerical and graphical descriptive analyses of the most commonly selected combinations of essential strategies, itemization of strategies qualifying as substitutes or compliments, the REE of each strategy, and Stage 2 importance and feasibility ratings of each strategy. During the interactive webinar, study investigators will facilitate a general discussion of the summary material provided to panelists in preparation for developing recommendations for which implementation strategies are essential at each of the three temporal phases in the particular scenarios. This will be followed by scenario-specific facilitated discussions of the top five essential strategy combinations obtained in Stage 3. Live polling will be used to document the degree of consensus for the final recommendations for each scenario. Polling will commence one scenario at a time, addressing each temporal phase of implementation separately, one conceptual cluster of strategies at a time, presenting the top five essential strategy combinations plus any additional combinations identified as highly preferable during the facilitated discussion. Poll results will be used to characterize the expert panel’s rate of consensus for the final set of recommendations regarding which discrete strategies are essential for each phase of implementation for a particular implementation scenario.

